| 
Procedures: Visits at days 7, 21, 14, 28, 90 and 365.
                                                                                                                                                                                                                                                                                                                                                                                                                                                                                                                                                                                                                |
| 
Duration of treatment = 2 hours, duration of surveillance per patient = 365 days
                                                                                                                                                                                                                                                                                                                                                                                                                                                                                                                                                                                     |
| 
Statistical Considerations: Intention to treat analysis, expected mortality at day 28 = 40%, expected relative reduction with study intervention = 30 %, <math>\alpha</math> = 5%, <math>\beta</math> = 20%, number of subject to include = 500. Interim analyses at 100, 200, 300 and 400 patients included.
                                                                                                                                                                                                                                                                                                                                                        |

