### 7.3. Endpoints

The principal endpoint will be vital status (dead/alive) at day 28

The secondary endpoints will be

- day-90 mortality
- number of ventilator-free days at day 28
- number of renal replacement therapy-free days at day 28
- number of vasopressors-free days at day 28
- use of ECMO before day 28
- value of the SOFA score at days 7, 14 and 28 [1] (see appendix A).
- changes in SOFA scores over the following 7, 14 and 28 days
- value of the SARS-CoV-2 viral load, expressed as cycle threshold, [2] in the tracheal aspirates (for intubated patients) or nasopharyngeal swabs (for extubated patients) at days 7, 14 and 28
- blood C reactive protein (CRP) concentrations at days 7, 14 and 28
- length of stay in the acute care hospital
- location of the patients at day 90: acute care hospital, post-acute care hospital, long-term residency, home
- WHO progression scale prior transfusion, at day 7 and at discharge (see appendix B)
- Hospital Activity of Daily Living (ADL) functional score at day 90 and at day 365. [3] (see appendix C).
- Anxiety-depression evaluation scale at day 90 and at day 365. [4] (see appendix D ).
- Quality of life scale (EQ-5D-5L) at day 90 and at day 365. [5] (see appendix E).
- Transfusion-related adverse events within 7 days
- Sero-positivity to SARS-CoV-2 at days 1, 7, 28 and 90
- Adverse events related to standard of care (mechanical ventilation, prolonged decubitus, prone positioning...) such as:
  - o Ventilator associated pneumonia
  - o Secondary bacteremia [6]
  - o Deep vein thrombosis and pulmonary embolism
  - o Pressure ulcers, stage 2 to 4 (*i.e.* loss of skin, of tissue or of bone) [7]
  - o Ventilator induced baro-traumatism (pneumothorax, pneumo-mediastinum, sub-cutaneous emphysema) [8]
  - o Accidental ablation of tracheal or vascular device [9]
  - o Ventilator induced baro-traumatism (pneumothorax, pneumo-mediastinum, sub-cutaneous emphysema) [8]
  - o Accidental ablation of tracheal or vascular device [9]

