### 9.3. Participants eligibility

#### 9.3.1 Inclusion criteria

We will include patients with the following criteria:

- age at least 18 years
- hospitalization in an intensive care unit participating to the study
- medical diagnosis with SARS-CoV-2 pneumonia as defined by both:
  - o extended interstitial pneumonia on CT scan or a chest X-ray, consistent with viral pneumonia, within 10 days prior to inclusion
  - o Positive result of SARS-CoV-2 PCR test, or any emerging and validated diagnostic laboratory test for COVID-19, within 15 days prior to inclusion
- under mechanical ventilation administered through an endotracheal tube, for no more than 5 days
- prior Clinical Frailty Scale < 6 [32] (see appendix F ).
- written consent of the patient, or – if impossible - of a relative acting as the legal representative, or – if impossible - of a physician from a non-participating department of the same hospital acting as an impartial witness (see trial procedures).

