### **9.5.3 Process of randomization**

The process of randomization will be performed through a standard randomization system (UCL clinical trial center, Pr [name]) either directly through the eCRF system or by the CCC St Luc. The randomization process will be stratified according to the delay from tracheal intubation to inclusion (" $\leq$  48 hours"; "between 48 hours and 5 days"). A response to telephone calls for any issue regarding the inclusion criteria will be available 24/7 (see "availability of the study product" paragraph).

The treatment (intervention versus control) will be allocated in 2 arms in a 1:1 ratio. The randomization table will be made of permuted block size provided by the statistician.

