## 9.9. Statistical Analysis

- Primary outcome

The primary outcome of the trial is mortality at day 28. Based on prior reports from China, Italy and UK, and consistent with personal observations, we anticipate that the mortality at day 28 will be around 40 %. As no comparative study has yet been published, the reduction that we anticipate is empiric. We consider that a one third relative reduction in 28-day mortality is realistic and clinically relevant. As this reduction might be greater, we plan to perform an interim analysis for ethical reasons. With a two-sided  $\alpha$ -risk of 0.05 and a  $\beta$ -risk of 0.20, the minimal number of patients to include to reach significance for a one third relative reduction in 28-day mortality (an absolute reduction of 13.5% day-28 mortality in the intervention group assuming a day-28 mortality of 40 % in the control group) is 250 in the control group and 250 in the active group (total number of patients = 500). This number allows for four interim analyses to be performed in addition to the final analysis, respectively after assessment of 100, 200, 300, 400 and 500 patients. Considering that others trials in COVID-19 may result in modification in mortality and therefore in standard of care, we anticipate that the number of patients that is necessary to address our hypothesis may vary, and will have to be adapted depending on the results of the interim analyses.

- Statistical analysis plan

Results will be analysed in intention to treat and expressed as means and standard deviations (SD) for quantitative variables with a Normal distribution and as medians and 25th to 75th percentiles for skewed distributed quantitative variables. Qualitative variables will be expressed using counts and percentages.

Mean values between groups will be compared by Student t-test but also by the non-parametric Wilcoxon test when normality assumption is not fulfilled. Proportions will be compared by the chi-square

test. Appropriate multivariate analyses will be performed to assess the relationship between outcome and patients' characteristics and clinical features.

For the primary endpoints, vital status at day 28 in all groups will be calculated with corresponding 95% CI. Comparison between groups will be tested using chi-square test.

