Regarding the secondary endpoints, quantitative values between groups will be compared by Student t-test or non-parametric Wilcoxon for the SOFA score (at different time points), viral load of SARS-CoV-2 (at different time points), circulating CRP (at different time points), ADL score at day 90, anxiety-depression scale at day 90, sero-conversion. Poisson regression analysis will be considered to analyse number of ventilator-free days up to day 28. Comparison of proportions will be applied to compare location of patient at day 90, as well as presence of various adverse events. If descriptive analysis revealed the presence of potential confounding factors, appropriate multivariate analysis will then be considered.

The two-sided level of significance used in this trial is 5%. Statistical analyses will be carried out using SAS (version 9.4 for Windows) statistical package.

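### Plain Poisson regression, the method Section 9.9 names for ventilator-free days, would give a false-positive rate of roughly 35% to 58% instead of 5% if run with model-based standard errors

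*Protocol*

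**What the plan says.** Section 7.3 of the protocol lists "number of ventilator-free days at day 28" among the secondary endpoints, and Section 7.2 makes a shorter duration of ventilation a secondary objective. In Section 9.9 most quantitative secondary endpoints (SOFA score, viral load, CRP, ADL, anxiety-depression) go to the Student t-test or the Wilcoxon test. Ventilator-free days are singled out: "Poisson regression analysis will be considered to analyse number of ventilator-free days up to day 28". The sentence mentions no dispersion parameter, robust variance or zero-inflation component. The same section states that "The two-sided level of significance used in this trial is 5" percent.

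Two other statements bear on the shape of this outcome. Patients enter while "under mechanical ventilation administered through an endotracheal tube, for no more than 5 days" (Section 9.3.1), so all are ventilated at inclusion. For the control group, "we anticipate that the mortality at day 28 will be around 40" percent (Section 9.9). The protocol gives no distribution for ventilator-free days and no rule for scoring deaths.

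**The concern.** A Poisson model derives its standard error from the assumption that the variance equals the mean. Ventilator-free days in this population are unlikely to behave that way. If deaths count as 0, about 40% of values are zero from mortality alone, survivors still ventilated at day 28 add more, and the rest spread over a bounded range of up to 28 days. A variance well above the mean makes the model-based standard error too small by the square root of their ratio. The P-value is then too small and the confidence interval too narrow.

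At stake is the interpretation of this one secondary endpoint. In an open-label trial with a neutral mortality result, a nominally significant effect on ventilator-free days would attract attention, and under this analysis it could easily be an artefact of the variance assumption.

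**Working it through.** **Inputs.** From the protocol: two-sided 5% level, 40% expected control mortality, all patients ventilated at entry, a 28-day horizon and 250 patients per arm. Section 9.9 assumes an absolute reduction of 13.5 points, so the lowest mortality it contemplates is 40% − 13.5% = 26.5%; I use this as the low end for the share of zeros. Assumed, because the protocol is silent: deaths score 0; 0 to 20 percentage points of extra zeros for survivors still ventilated at day 28 (up to 60% zeros in all); and several shapes for the non-zero values.

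**The plan's own figure.** The only figure that applies to this test is the 5% level. When the data really are Poisson (mean 8), the simulated false-positive rate is 5.4% and the analytic rate 5.0%, so the calculation behaves correctly where the model holds.

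**Dispersion.** Let z be the share of zeros, and m and s² the mean and variance of the non-zero values. Then:

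- mean = (1 − z)m
- variance = (1 − z)s² + z(1 − z)m²
- dispersion φ = variance / mean = s²/m + z·m

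For values uniform over the integers a to b, m = (a + b)/2 and s² = ((b − a + 1)² − 1)/12.

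**False-positive rate.** The two-arm Poisson Wald test divides the log ratio of means by √(1/S₁ + 1/S₂), where S₁ and S₂ are the arm totals. The true standard error is √φ times larger, so the actual two-sided rate is 2[1 − Φ(1.96/√φ)]. This does not depend on sample size.

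**Worked case: 40% zeros, rest uniform over 1 to 27.** m = 14 and s² = (27² − 1)/12 = 60.67. φ = 60.67/14 + 0.40 × 14 = 4.33 + 5.60 = 9.93, and √φ = 3.15. 1.96/3.15 = 0.62, giving a rate of 53%. Simulating 20,000 null trials with 250 per arm gave 53.3%.

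**Other cases, same formula.**

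| Zeros | Non-zero values | φ | √φ | False-positive rate |
|---|---|---|---|---|
| 26.5% | uniform 1–15 | 4.45 | 2.11 | 35% |
| 26.5% | uniform 10–24 | 5.60 | 2.37 | 41% |
| 26.5% | uniform 1–27 | 8.04 | 2.84 | 49% |
| 40% | uniform 1–20 | 7.37 | 2.71 | 47% |
| 40% | uniform 10–25 | 8.21 | 2.87 | 49% |
| 50% | uniform 1–27 | 11.33 | 3.37 | 56% |
| 60% | uniform 1–27 | 12.73 | 3.57 | 58% |

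**A floor that needs no shape.** Since s²/m cannot be negative, φ is at least z·m. With 40% zeros and a non-zero mean of 14 days, φ ≥ 5.6 and the rate is at least 41%. With a mean of 10 days, φ ≥ 4 and it is at least 33%. With a mean of 5 days, φ ≥ 2 and it is at least 17%.

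**Less favourable shapes for the argument.** With 40% zeros and non-zero values confined to 1–10 days, the simulated rate is 31%; with all of them at exactly 5 days it is 16%. With no excess zeros (uniform 0–28) it is 38%. The inflation shrinks but does not disappear.

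**After repair.** On the simulated zero-heavy data, a Pearson-scaled or sandwich standard error gives 4.5% to 5.4%. The Wilcoxon test under comparable scenarios gives about 4% to 5.5%.

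**The case against.** The strongest reply is that the protocol does not commit to the analysis criticised here. Poisson regression is only to be considered, no standard-error type is stated, and a statistical analysis plan could specify a scaled or robust variance that restores the error rate. Section 9.9 also has a general provision for the Wilcoxon test when normality fails, which could serve as a fallback. This stands in part: every rate above depends on Poisson being adopted and run with model-based standard errors. It does not remove the point. The sentence picks this endpoint out for a specific model and names no alternative for it, and that model in its plain form does not fit. This is a poor stated choice, not a detail left for later.

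A reader might infer more than the documents support:

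- **That the error rate is simply 50%.** The protocol gives no distribution and no scoring of deaths, so only a conditional range can be stated.
- **That this is the main respiratory secondary endpoint.** Section 7.3 lists it among many and ranks none of them.
- **That treating a death like a survivor still ventilated at day 28 is a fault of Poisson regression.** That comes from scoring deaths as 0, and a Wilcoxon test on the same values would share it. Ranking deaths below 0 is a design preference. That early deaths might earn free days is speculation from silence, and a scoring rule is ordinary analysis-plan content.
- **That renal-replacement-free and vasopressor-free days have the same problem.** Section 9.9 does not name Poisson regression for either.

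**Conclusion.** The method is wrong as written. If deaths score 0 and model-based standard errors are used, the variance of ventilator-free days is roughly 4 to 13 times the mean. The two-sided false-positive rate is then roughly 35% to 58% instead of 5%, about 53% in the worked case, and confidence intervals are about 2 to 3.5 times too narrow. The rate would be lower only if non-zero patients had very few free days, and even then it stays well above 5%.

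The chi-square test of day-28 mortality and the interim rules rest on mortality alone and are unaffected. The point should be fixed, but it does not endanger the trial's primary conclusion.

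**What to change.** In Section 9.9, replace the Poisson sentence with one of two choices:

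- Compare ventilator-free days by the Wilcoxon rank-sum test, as for the other quantitative secondary endpoints. It may optionally be stratified by the randomisation stratum, delay from intubation to inclusion.
- If a ratio of mean days is wanted, keep the log-linear model and state that standard errors come from a sandwich or Pearson-scaled variance.

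Either brings the error rate back to about 5%. The cost is one sentence, with no new data collection. The rank test does not yield a ratio of mean days; the second choice keeps it.

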#### – Interim analysis plan

Due to ethical considerations of the current situation, we propose to conduct a group-sequential design with several interim analyses. The objective of including interim analyses in the study design is to allow the possibility of stopping the study early if a clinically relevant benefit is already established from a statistical point of view. Conversely, the interim analyses also allow the possibility of an early stopping of the study if the observed benefit, at the time of the interim analysis, is so small as to make it extremely unlikely that the study would succeed, were it continued until full accrual. Finally, the interim analyses will also include a futility stopping rule for the SOC group, which may appear to be unjustified if mortality in that group appears too large to be acceptable.

Specifically, the interim assessment of the SOC group will be based on the numbers of patients and of deaths shown in Table 1. The recommendation will be made to stop accruing patients in the SOC group if the number of deaths observed in this group suggests a true mortality rate in excess of 0.4. The rule for DSMB recommendation shown in Table 1 will not be binding.

**Table 1:** interim analysis and potential recommendation of the DSMB to stop the SOC group

| Interim analysis | Number of patients in SOC group | Recommend to stop SOC group if number of deaths | Probability of seeing this number of deaths if true mortality rate $\leq 0.4$ |
|------------------|---------------------------------|-------------------------------------------------|-------------------------------------------------------------------------------|
| 1                | 25                              | $\geq 14$                                       | $< 0.034$                                                                     |

|   |     |           |           |
|---|-----|-----------|-----------|
| 2 | 50  | $\geq 26$ | $< 0.031$ |
| 3 | 75  | $\geq 37$ | $< 0.04$  |
| 4 | 100 | $\geq 48$ | $< 0.042$ |

The interim analyses will be performed with 100, 200, 300 and 400 patients evaluable for 28-day mortality. Two Lan-Demets spending functions will be used: one, similar to a Pocock (aggressive) boundary to stop the study for futility, and the other, similar to an O'Brien-Fleming (conservative) boundary to stop the study for extreme efficacy. If the interim analyses take place with increments of exactly 100 patients, and assuming a mortality of 40% in the control group, the recommendations to stop the study for futility or for efficacy are summarized in Table 2. Of note, the trial will reach statistical significance if the absolute difference in 28-day mortality is 9% or larger, which might still be a clinically worthwhile difference. The rules for DSMB recommendations shown in Table 2 will not be binding.

**Table 2:** interim analyses and potential recommendations of the DSMB to stop the trial for futility or efficacy, depending on the observed treatment effect (and associated P-value)

| Interim analysis | Number of patients | Recommend stopping for futility if difference in mortality is smaller than | Recommend stopping for efficacy if difference in mortality is greater than |
|------------------|--------------------|----------------------------------------------------------------------------|----------------------------------------------------------------------------|
| 1                | 100                | 0.02 ( $P > 0.83$ )                                                        | -                                                                          |
| 2                | 200                | 0.04 ( $P > 0.60$ )                                                        | 0.22 ( $P < 0.001$ )                                                       |
| 3                | 300                | 0.06 ( $P > 0.28$ )                                                        | 0.14 ( $P < 0.007$ )                                                       |
| 4                | 400                | 0.08 ( $P > 0.12$ )                                                        | 0.11 ( $P < 0.022$ )                                                       |
| 5 (final)        | 500                | -                                                                          | 0.09 ( $P < 0.042$ )                                                       |

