## 8. Background Information and Scientific Rationale

The COVID-19 pandemic started in China in December 2019 and spread to European countries in early 2020, affecting most severely Italy, Spain and France. Belgium was affected during the same wave and first deaths due to COVID-19 were reported in early March 2020. As of September 10, 2020, almost 28 million cases, including 900,000 deaths, have been confirmed over the world and almost 90,000 cases, including 9,900 deaths, have been declared in Belgium [10].

Current data from the Belgian surveillance system indicate that 20% of the hospitalized patients are in ICUs [11]. Hospital deaths occur either in the ICU (13 / 31, 31 % in Liège University Hospital, personal data) or in non-ICU wards for those patients who would not benefit from intensive care as anticipated by the medical team [12]. Based on United Kingdom ICNARC reports, and according to personal observations in Belgium, the COVID-19 ICU patients require mechanical ventilation in 60% of cases, particularly when they are referred directly by the emergency medical service. According to different series, forty to sixty percent of the mechanically ventilated patients are likely to die, most of them when mechanical ventilation is instituted early (30% survival rate) rather than late in the course of the disease (70 % survival rate) [13]. Similar observations have been made in China [14]. Besides the direct cost in human lives, the current situation in European countries has led to a halt in most of medical and scheduled surgical practices for non COVID-19 patients and to a doubling of the number of ICU beds. The nursing and medical manpower per patient in ICUs has also been doubled due to the intensity of care that patients require with the use of invasive ventilation and the practice of alternate prone positioning for severe ARDS [15].

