### 9.2. Description of population

- The study population will be patients with SARS-CoV-2 pneumonia associated with acute respiratory failure and requiring mechanical ventilation
- Number of patients planned: 500 (1 intervention group of 250; 1 control group of 250)

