## 9.10. Changes in the Conduct of the Study or Planned Analyses

- Provision for adaptive design changes at the time of interim analyses

Because of the considerable uncertainties about the outcomes that will be observed in the three arms of the trial, the DSMB will be allowed to recommend design changes based on the observed data at the times of the interim analyses. These changes may include an adaptation of the sample size or the patient selection. Any such changes are adaptive in nature and will be implemented using appropriate methods to control the impact of these changes on the operating characteristics of the trial (especially the probability of type I error).

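### Table 1, the non-binding rule for stopping the SOC group, assumes half the SOC patients that 1:1 allocation gives, and its printed probabilities are those of one death more than its limits

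*Protocol*

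**What the plan says.** The design has two arms. Section 9.5.3 states: "The treatment (intervention versus control) will be allocated in 2 arms in a 1:1 ratio". Section 9.2 plans "500 (1 intervention group of 250; 1 control group of 250" patients. Under the interim analysis plan in section 9.9, "The interim analyses will be performed with 100, 200, 300 and 400 patients evaluable for 28-day mortality".

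The same plan adds a rule for the SOC group alone. The DSMB's recommendation would be: "stop accruing patients in the SOC group if the number of deaths observed in this group suggests a true mortality rate in excess of 0.4". Table 1 has a column headed "Number of patients in SOC group" and gives, for interims 1 to 4:

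| Interim | SOC patients | Stop SOC if deaths | Printed probability if true mortality is at most 0.4 |
|---|---|---|---|
| 1 | 25 | 14 or more | < 0.034 |
| 2 | 50 | 26 or more | < 0.031 |
| 3 | 75 | 37 or more | < 0.04 |
| 4 | 100 | 48 or more | < 0.042 |

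The text describes this rule as not binding. Table 2, also non-binding, separately monitors the difference in mortality between the arms. Section 9.10 refers to "outcomes that will be observed in the three arms of the trial". The planning rate for control mortality in section 9.9 is about 40%, and section 8 reports that "forty to sixty percent of the mechanically ventilated patients are likely to die".

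**The concern.** A DSMB given Table 1 cannot apply it as printed. At interim 1 the table expects 25 SOC patients, but the design delivers about 50, so the interim number and the SOC count point to different rows. The false-signal probability beside each limit also looks too small for the limit it accompanies.

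The action attached to the table makes this matter. With only two arms, a DSMB recommendation that was followed would end concurrent randomisation, and the rule reaches that recommendation without looking at the plasma arm. Patients already randomised could still be compared, but on fewer data than planned. The reference value of 0.4 is also the planning rate itself and the lower end of the range quoted in section 8. A control arm that behaves as the background section allows could therefore trigger the rule.

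**Working it through.** **Inputs.** Two arms at 1:1 (9.5.3), 250 per arm (9.2), interims at 100, 200, 300 and 400 evaluable patients (9.9), Table 1 limits k and sizes n (9.9), reference mortality 0.4 (9.9), background range 40 to 60% (section 8).

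**Step 1: SOC sizes.** At 1:1 the expected SOC number is half the total: 100/2 = 50, 200/2 = 100, 300/2 = 150, 400/2 = 200. Table 1 has 25, 50, 75 and 100, a quarter of each total. Three equal arms would give about 33, 67, 100 and 133, so the wording in 9.10 does not explain the table either.

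**Step 2: printed probabilities.** With X ~ Binomial(n, 0.4), I computed the tail for the rule as printed, P(X ≥ k), and for the strict inequality, P(X > k) = P(X ≥ k + 1).

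| n | k | Printed | P(X > k) | P(X ≥ k) | P(X ≥ k) / printed |
|---|---|---|---|---|---|
| 25 | 14 | 0.034 | 0.0344 | 0.0778 | 2.3 |
| 50 | 26 | 0.031 | 0.0314 | 0.0573 | 1.8 |
| 75 | 37 | 0.04 | 0.0396 | 0.0637 | 1.6 |
| 100 | 48 | 0.042 | 0.0423 | 0.0638 | 1.5 |

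The strict inequality reproduces all four printed values to rounding. A normal approximation to P(X ≥ k) does not: it gives 0.051, 0.042, 0.050 and 0.051 without continuity correction, and 0.077, 0.056, 0.063 and 0.063 with it. The table is therefore off by one death.

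**Step 3: cumulative chance of a stop recommendation at the table's own sizes.** This adds independent binomial increments of 25 patients between looks and removes paths that have already crossed.

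| True SOC mortality | Limits as printed (14, 26, 37, 48) | Limits that match the printed probabilities (15, 27, 38, 49) |
|---|---|---|
| 35% | 3.6% | 1.5% |
| 40% | 15.0% | 8.9% |
| 45% | 43.0% | 32.5% |
| 50% | 76.9% | 68.4% |
| 60% | 99.6% | 99.3% |

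At 40% mortality the off-by-one error accounts for 15.0 − 8.9 = 6.1 percentage points. The remainder comes from taking four looks at 3 to 4% each.

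**Step 4: printed counts applied to the patients actually present.** If 14 deaths were read against the roughly 50 SOC patients at interim 1, P(X ≥ 14 | n = 50) is 0.972 at 40% mortality and 0.672 at 30%. Fourteen of 50 is 28% observed mortality.

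**Step 5: limits at the sizes the design gives.** Keeping per-look tails at 40% mortality close to the printed 0.03 to 0.04:

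| SOC patients | Deaths | P(X ≥ limit) at 0.4 |
|---|---|---|
| 50 | ≥ 27 | 0.031 |
| 100 | ≥ 49 | 0.042 |
| 150 | ≥ 71 | 0.041 |
| 200 | ≥ 93 | 0.036 |

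The cumulative chance over the four looks is 9.0% at 40% mortality and 89% at 50%. At 200 patients, a limit of 92 also has a tail below 0.05 (0.049); 93 stays nearer the printed level.

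**The case against.** The strongest defence is that the rule is explicitly non-binding, so nothing stops automatically and the DSMB would see the whole picture. That stands, and the consequence must be stated as conditional on the recommendation being followed. It does not repair the table, because the DSMB would still be weighing wrong sizes and understated probabilities.

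A reader might infer that the rule would very likely close the control arm, citing the 97% in step 4. The documents do not support that as a property of the plan. Table 1 ties each death count to its own number of SOC patients, and the text asks for deaths that suggest mortality above 0.4, which 14 of 50 does not. The 97% shows what a misreading would cost. On the table's own terms the figure at the planned mortality is 15%. Nor does the off-by-one error produce a near-certain stop.

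The figures at 45% and above are not false signals, since true mortality there does exceed 0.4. They bear on the choice of 0.4 as the reference, which the protocol makes on ethical grounds. That is a design judgement, and it does not by itself show that the rule should be removed. That the table was carried over from another design is likewise a guess.

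**Conclusion.** Table 1 is wrong as written on two counts, both reproducible from the protocol. The SOC sizes are half of those the allocation and interim schedule imply, and the printed probabilities belong to limits one death higher. Per-look false-signal rates at 40% mortality are 1.5 to 2.3 times those stated. At the table's own sizes the cumulative chance of a recommendation to stop SOC is 15% at 40% mortality, 43% at 45% and 77% at 50%. The mention of three arms in 9.10 contradicts the two-arm design.

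These figures assume independent patients with a common mortality, looks at exactly the stated sizes, and a rule applied at every interim. The SOC counts of 50, 100, 150 and 200 are expected values; permuted blocks would keep the actual numbers close to them. Because the table is a stopping guide for one of only two arms, it should be corrected before the DSMB uses it.

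**What to change.** Restate Table 1 at 50, 100, 150 and 200 SOC patients, with exact binomial limits and probabilities computed for the same inequality as the rule. One set that keeps the per-look level near that printed is the one in step 5. State the criterion used to choose the limits, and give the cumulative probability over the four looks beside the per-look values. In section 9.10, change three arms to two.

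Correct arithmetic alone leaves a rule that would fire often if control mortality is near 50%. The sponsor and DSMB should therefore reconcile the SOC-stopping passage with the two-arm design, the 40% planning rate, the 40 to 60% range in section 8 and the between-arm monitoring in Table 2, and say what happens to the trial if SOC accrual stops. Whether to keep, change or drop the rule is for them to decide.

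The cost is an amendment to the protocol and the DSMB's working documents, with no extra patients or data.
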